### Sample size

3.4

To ensure that the study is adequately powered, we have estimated the sample size based on the primary outcome of absolute difference in CAC score at 18-months between the control and intervention arms, assuming mean CAC scores at 18-months of 1005 and 786 respectively as reported by Block et al.^[19]^ Applying natural logarithmic transformation to CAC scores due to skewed distribution, this corresponds to a mean logCAC of 6.91 and 6.67, respectively. Further assuming a common SD of 0.55, power of 80%, 2-sided level of significance of 5% and equal allocation between the 2 treatment arms, a minimum sample size of 170 in total, or 85 per arm will be required. Accounting for an attrition rate of 15%, we will recruit a total of 200 patients.

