### Eligibility criteria:

3.2

Patients meeting the inclusion and exclusion criteria will be invited to participate and written informed consent obtained for those willing to participate. Consented subjects will attend a screening visit (V0) where a multislice computed tomogram will be performed to assess their degree of CAC. As the main objective is to investigate the effects of intervention on VC, pre-existing CAC indicated by a baseline CAC score of ≥ 30 Agatston units is mandated for entry into the trial. This threshold also excludes patients with mild CAC which is unlikely to progress in the relatively short window of observation.^[19]^ Other inclusion and exclusion criteria are outlined in Table 1. Consent is taken by study team co- investigator after detailed explanation of purpose, benefit and risk of the study. Witness is required for patient signing informed consent in Chinese and Malay language. Patients are informed the right to withdraw consent and participation at any time during the study period.

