### Study outcomes

3.8

Control and intervention arms will be compared for the following outcomes of interest:

Primary outcome

Absolute difference in CAC score at 18-months

Secondary outcomes

(1)Absolute difference in AVC score at 18-months(2)Percentage of patients with regression of CAC of ≥ 10% over 18-month(3)Absolute difference in cfPWV and AI at 18-months(4)Mortality from any cause within the study period(5)MACE defined as non-fatal myocardial infarction, heart failure, acute coronary syndrome, need for coronary revascularization, non-fatal stroke, significant peripheral vascular disease (gangrene, amputation, need for revascularization) within the study period(6)Difference in plasma levels of dp-ucMGP at 18 months(7)Vascular access events, including clotting requiring insertion of a new dialysis catheter, declotting or exchange of an existing catheter, and vascular intervention during the study period.

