### Statistical methods

3.9

The absolute difference in CAC and AVC scores at 18-months between control and intervention arms will be compared using the t-test following log transformation. Adjustment for baseline CAC and AVC scores respectively will be made via the analysis of covariance. Likewise, the effects of MK-7 supplementation on dp-ucMGP level, CFPWV and AI at 18 months will be compared between the 2 groups using the t-test, with adjustment made for the respective baseline covariates via analysis of covariance.

The percentage of patients with regression of CAC score of ≥ 10% at 18 months from baseline will be compared between control and intervention arms via the χ^2^ test. The effect of treatment will be quantified using the odds ratio estimate and its associated 95% confidence interval. The logistic regression analysis will be used to account for potential confounders where applicable.

For all-cause mortality and MACE, the time to the respective event is defined as the time from randomization to the time when the event of interest occurred. Subjects in whom an event was not observed will be censored at 18-months. The Kaplan-Meier survival analysis and the log-rank test will be used to compare the survival distributions between the control and intervention groups. The effect of treatment will be quantified using the hazard ratio estimate and its associated 95% confidence interval. Further, the Cox proportional hazards regression stratified by diabetes will be used to account for potential confounders where applicable.

All statistical evaluations will be made assuming a 2-sided test at the 5% level of significance based on an intention-to-treat analysis.

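### The log SD of 0.55 behind the 80% power is unsourced and hard to square with a 30 AU entry threshold, and neither the unadjusted t-test nor the baseline-adjusted ANCOVA is named as the primary test

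*Protocol article*

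**What the plan says.** All references are to the protocol article.

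- **3.8 Study outcomes.** The primary outcome is "Absolute difference in CAC score at 18-months", compared between arms.
- **3.4 Sample size.** The calculation proceeds by "assuming mean CAC scores at 18-months of 1005 and 786 respectively" for control and intervention, and says "this corresponds to a mean logCAC of 6.91 and 6.67, respectively". It continues: "Further assuming a common SD of 0.55, power of 80%, 2-sided level of significance of 5" per cent. The result is 85 per arm, 170 in total, raised to 200 for 15% attrition. No baseline correlation enters. The text does not say where 0.55 comes from, or whether it is a between-patient SD or a residual SD after baseline adjustment.
- **3.2 Eligibility criteria.** Here "a baseline CAC score of ≥ 30 Agatston units is mandated for entry into the trial". The section adds that this cut-off removes patients whose mild calcification would probably not progress during follow-up.
- **3.3 Study interventions.** Randomization is stratified by diabetes.
- **3.9 Statistical methods.** The first sentence reads: "The absolute difference in CAC and AVC scores at 18-months between control and intervention arms will be compared using the t-test following log transformation". The next reads: "Adjustment for baseline CAC and AVC scores respectively will be made via the analysis of covariance". Neither is called primary. Diabetes appears in this section only as a stratum of the Cox model for mortality and cardiovascular events.

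**The concern.** The calculation in 3.4 has the form of a two-sample comparison without baseline, so 0.55 acts as the spread of log scores between patients at 18 months. That is narrow for a trial that admits anyone scoring 30 AU or more and assumes a control mean of about 1000 AU. If the true spread is wider, the unadjusted t-test has less power than stated, and a null t-test could be read as evidence against MK-7 when the test may have had less than an even chance of detecting the planned effect.

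The second issue adds to the first. Section 3.9 gives two analyses of one primary outcome whose power can differ greatly and does not say which one decides the trial. The trial is open-label and, according to section 5, all final visits are complete. The choice should therefore be on record before any comparison by arm.

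**Working it through.** **1. Reproduce the plan's figure.** Inputs from 3.4: ln 1005 = 6.913 and ln 786 = 6.667, rounded there to 6.91 and 6.67; difference 0.24; SD 0.55; two-sided alpha 0.05; power 80%.

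n per arm = 2 × (1.960 + 0.842)² × 0.55² / 0.24² = 82.4, so 83. The t-distribution version gives 84. The plan's 85 agrees within two patients. Power at 85 per arm is 81.2% (normal) or 80.7% (t). Attrition: 170 / 0.85 = 200. The unrounded difference of 0.246 would give 79 to 80 per arm, so the rounded logs were used.

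The plan takes the log of a mean as the mean of the logs. With a common log SD this shifts both arms equally and leaves the difference unchanged.

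**2. What an SD of 0.55 implies.** Take 6.91 as the control mean log and assume normality on the log scale.

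- 95% range: exp(6.91 ± 1.96 × 0.55) = 341 to 2945 AU.
- Distance of 30 AU (ln 30 = 3.40) below the mean: (6.91 − 3.40) / 0.55 = 6.4 SD.
- Distance of 100 AU (ln 100 = 4.61) below the mean: (6.91 − 4.61) / 0.55 = 4.2 SD, a probability of about 1.4 in 100,000.

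If 1005 is instead the arithmetic mean, the mean log is 6.913 − 0.55²/2 = 6.76. The range becomes 294 to 2539 AU and the probability of a score below 100 is about 4 in 100,000. The picture is the same.

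**3. Unadjusted t-test over a range of SDs.** 85 per arm, difference 0.24, noncentral t. Every SD other than 0.55 is an assumption, because the article gives no alternative.

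| Log SD | Power |
|---|---|
| 0.55 | 81% |
| 0.7 | 60% |
| 0.8 | 49% |
| 1.0 | 34% |
| 1.2 | 25% |
| 1.5 | 18% |

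**4. ANCOVA on log baseline.** Residual SD = s × √(1 − r²), where s is the between-patient log SD and r the correlation of log CAC between baseline and 18 months. Both are assumed. Power at 85 per arm, normal approximation:

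| s | r = 0.80 | r = 0.90 | r = 0.95 | r needed for residual SD 0.55 |
|---|---|---|---|---|
| 1.0 | 74% | 95% | >99% | 0.84 |
| 1.2 | 58% | 85% | 99% | 0.89 |
| 1.5 | 41% | 67% | 92% | 0.93 |

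The last column is √(1 − (0.55/s)²); for s = 1.0 it is √(1 − 0.3025) = 0.835. ANCOVA is well ahead of the t-test in every row, but reaches 80% only when the correlation is high enough.

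**The case against.** **The threshold does not contradict the SD.** A lower limit on baseline scores is compatible with any SD of 18-month scores, including 0.55. The limit describes who is removed from the screened pool, not the spread of those enrolled. This stands, and a reader who infers that 3.2 refutes 3.4 goes too far. What remains is implausibility: under the distribution in 3.4, a patient near the threshold hardly exists, yet 3.2 relies on that threshold to remove mild disease.

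**The power shortfall is conditional.** On the plan's own inputs the t-test has its stated power, and the source of 0.55 cannot be checked from the article. This stands too. The top of the assumed range is also stretched. With an arithmetic mean of 1005, an SD of 1.5 puts about 6% of scores below 30, and imposing the floor at 18 months would cut the SD to about 1.34. The losses at 0.7 to 1.0 do not depend on that end of the range.

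**ANCOVA is already planned.** Section 3.9 commits to it, and a fuller analysis plan may say which test is primary. That is fair, and it lowers the weight of the point. Still, the article itself puts the unadjusted test first and gives two analyses without ranking them.

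**Raw or log baseline.** A reader might infer that the covariate is the untransformed score. The sentence follows directly on one about log transformation and does not specify the scale, so the text supports only a request to state it.

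**Too late to matter.** Recruitment is over, so restating power cannot change the sample, and a null result would be read mainly from its confidence interval. Fixing the primary test before the arms are compared still matters.

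**Conclusion.** The concern holds as a matter of plausibility and clarity, not as a demonstrated error. The stated sample size and power reproduce. The SD behind them is unsourced, its meaning is not stated, and it looks small for the population admitted. If it is really a between-patient SD and the true value is 0.8 to 1.0, the unadjusted t-test has 49% to 34% power. If it was meant as a residual SD, the 80% belongs to ANCOVA and not to the t-test.

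The article does not show that the trial is badly underpowered, because every alternative SD and correlation above is assumed. Nor does it show that ANCOVA restores 80%: that needs a correlation of about 0.84 at SD 1.0 and 0.93 at SD 1.5.

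The part that needs no assumed SD is that 3.9 leaves the primary test open and omits the stratification factor from the CAC analysis. Naming a log-baseline ANCOVA as the single primary test removes a choice between results and, where baseline and 18-month scores are strongly correlated, gains precision.

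**What to change.** - **3.9, primary analysis.** Name one: ANCOVA of ln(18-month CAC) on arm, ln(baseline CAC) and diabetes. Make the unadjusted t-test supportive only.
- **3.9, aortic score (AVC).** State the log baseline as covariate in the same way.
- **3.4.** Give the source of 0.55, say whether it is a between-patient SD or a residual SD after baseline adjustment, and state that the 80% power holds only for the analysis to which that SD applies.

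The cost is wording in two sections, settled before the arms are compared. Baseline CAC is already measured at the screening visit and diabetes status is already used in randomization, so no new data or patients are needed and the sample size stays as it is. The price is that the power claimed for the t-test may have to be stated less favourably.

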### Study workflow

3.5

Randomized patients will be scheduled for a first visit (V1) within 4 weeks from V0, during which blood will be drawn for dp-ucMGP, the biomarker of vitamin K deficiency, and aortic stiffness measured. Patients who are randomized to the treatment arm will receive MK-7 during this visit.

During the treatment phase of 18 months, the primary physician will review the study subjects at intervals of 2-6 months as per standard care. The research coordinator will contact these subjects every month to motivate compliance with active treatment, and perform pill counts during clinic visits to verify adherence. The investigational product (vitamin K2 isoform MK-7) will be stored in accordance to manufacturer's recommendations at Investigational Medicine Unit, National University Hospital Singapore.

Active treatment will end after 18 months, following which an end of study visit (V2) will be scheduled for all study subjects within 4 weeks. During V2, blood will be obtained for dp-ucMGP, and measurement of aortic stiffness and CAC/AVC scores repeated. The trial flow chart and study schedule is summarized in Figures 1 and 2 respectively.

**Figure 1 F1:**
[figure not shown]
Flow chart of the trial.

**Figure 2 F2:**
[figure not shown]
Study schedule of assessment.

The criteria for termination of the study are:

(1)Withdraw consent(2)completion of the study protocol at 18 months(3)renal transplantation(4)mortality(5)requirement for Vitamin K antagonist(6)allergy to MK-7(7)parathyroidectomy(8)started on any vitamin K supplementation outside of clinical trial

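### The termination criteria list post-randomisation events as ends of the study while the only outcome scan is at 18 months, which conflicts with the promised intention-to-treat analysis

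*Protocol article*

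**What the plan says.** Four places in the protocol article bear on this.

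- **Termination criteria (after Figure 2, section 3.5).** Eight criteria are said to terminate the study. Withdrawn consent, completion at 18 months, renal transplantation, death and need for a vitamin K antagonist come first. The list ends "allergy to MK-7(7)parathyroidectomy(8)started on any vitamin K supplementation outside of clinical trial".
- **Study workflow (3.5).** CAC/AVC scores, aortic stiffness and dp-ucMGP are measured after baseline only at V2, within four weeks of the end of the 18 months. That visit is to be scheduled for every subject. The text does not say whether this includes someone who has met a termination criterion.
- **Statistical methods (3.9).** Eighteen-month CAC, AVC, stiffness and dp-ucMGP are compared by t-test with ANCOVA for baseline, and CAC regression by chi-square. For mortality and MACE, anyone without an event is censored at 18 months. The section closes: "All statistical evaluations will be made assuming a 2-sided test at the 5% level of significance based on an intention-to-treat analysis".
- **Sample size (3.4).** "a minimum sample size of 170 in total, or 85 per arm will be required", and then "Accounting for an attrition rate of 15%, we will recruit a total of 200 patients".

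**The concern.** Intention-to-treat keeps patients in their randomised arm whatever happens afterwards. That includes stopping MK-7 because of allergy and taking vitamin K from another source. The termination list treats these same events as exits. If an exit means no V2, the t-test, ANCOVA and chi-square can use only patients who met none of the criteria before 18 months.

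Two features make this more than a matter of labels. First, some exits depend on arm. MK-7 allergy can arise only where MK-7 is given. Outside vitamin K is plausibly commoner among controls, who know in an open-label trial that they receive none; section 4 notes that supplements are sold over the counter. Second, exits that can occur in both arms (parathyroidectomy, vitamin K antagonist, transplantation) may be related to calcification. The introduction itself links hyperparathyroidism to it. Losing such patients selectively weakens the protection that randomisation gives the primary comparison.

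**Working it through.** **1. What the termination list means.** It could be read as rules for stopping treatment only. Against that, the same list contains death, withdrawn consent and completion, which are ways of leaving the trial. Completion is one exit, and the others are exits without completion. With a single post-baseline scan at 18 months, leaving earlier means no outcome value on the natural reading. The scheduling of V2 for every subject points the other way, and nothing in the article decides between the two.

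**2. The plan's own sample size.** Inputs from section 3.4: "this corresponds to a mean logCAC of 6.91 and 6.67, respectively", so the difference is 6.91 − 6.67 = 0.24; "Further assuming a common SD of 0.55"; two-sided 5%; power 80%; 1:1 allocation.

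- n per arm = 2 × (1.960 + 0.842)² × 0.55² / 0.24² = 82.4, so 83 per arm (166 in total). The noncentral-t version gives 84 per arm (168). The stated 170 is reproduced within 3%.
- 170 / (1 − 0.15) = 200, exactly as stated.
- Power is 81.2% with 170 evaluable patients and 87.0% if all 200 had a V2 scan.

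There is no arithmetic error. The attrition allowance protects power; it does not protect against selective loss.

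**3. Bias from selective loss.** The documents give no event rates, so the inputs here are assumptions. Let f be the extra share lost in one arm and k the number of SDs by which those lost differ from those kept. The full-arm mean minus the kept mean is then f × k × SD, which is the bias in the log difference. For type I error, take 85 per arm: SE = 0.55 × √(2/85) = 0.0844, and the error rate is Φ(−1.96 + bias/SE) + Φ(−1.96 − bias/SE).

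| f | k | Bias = f × k × 0.55 | Share of 0.24 | True type I error |
|---|---|---|---|---|
| 2% | 0.25 | 0.003 | 1% | 5.0% |
| 5% | 0.5 | 0.014 | 6% | 5.3% |
| 10% | 0.5 | 0.028 | 11% | 6.2% |
| 10% | 1.0 | 0.055 | 23% | 10.0% |
| 15% | 1.0 | 0.083 | 34% | 16.5% |

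The formula gives no credit for the baseline ANCOVA, which would remove the part of the selection explained by baseline CAC.

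**4. Time-to-event outcomes.** If follow-up really ends at a termination criterion, censoring at 18 months adds event-free time that nobody observed. A patient leaving at month 6 (an illustrative figure) would contribute 18 − 6 = 12 unobserved months. If follow-up continues instead, the censoring rule fits these patients but the termination list does not describe what is done.

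**The case against.** The strongest reply is that the article never says these patients miss V2. Section 3.5 schedules it for every subject, section 5 reports that all patients have completed their final visit, and the flow chart and assessment schedule are not visible here. This stands to the extent that a completer analysis is the natural reading, not a stated fact. It does not remove the conflict: the list still ends the study for these patients, and the statement in section 5 may refer only to those who remained.

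A second reply is that handling of missing data belongs in an analysis plan that is not shown. That is correct, and its absence is not the point. The point is a stated rule that conflicts with a stated analysis. Imputation could soften the consequence, but it would replace outcomes that could have been measured.

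Two stronger readings are tempting and are not supported:

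- **That all these exits depend on arm.** A reader might infer this from the list. Only MK-7 allergy is necessarily confined to one arm. Outside vitamin K is plausible but undocumented. The documents give no reason to expect imbalance in vitamin K antagonist use, parathyroidectomy or transplantation.
- **That the bias could be half the planned effect.** Putting the whole 15% attrition into the formula with a gap of 0.8 log units gives 0.15 × 0.8 = 0.12, or 50% of 0.24; a gap of 0.3 gives 0.045, or 19%. But the 15% is not itemised and must also cover deaths and withdrawn consent. A gap of 0.8 is 0.8 / 0.55 = 1.45 SD, and nothing in the article supports either gap.

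**Conclusion.** The concern holds as a conflict between the termination list, the V2 schedule in section 3.5 and the intention-to-treat statement in section 3.9. Followed as written, the rules drop patients from the 18-month comparisons because of what happened after randomisation. The 18-month censoring rule does not fit anyone whose follow-up ended earlier without an event.

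The size is unknown. Over the assumed range (2% to 15% excess loss in one arm, 0.25 to 1.0 SD difference) the bias is 0.003 to 0.083 on the log scale, or 1% to 34% of the planned 0.24. At the mild end, such as 5% at 0.5 SD, it hardly matters. The finding therefore rests on the contradiction and on who enters the primary comparison; no bias has been demonstrated. The sample size is unaffected.

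**What to change.** Reconcile sections 3.5 and 3.9 by stating that transplantation, vitamin K antagonist need, MK-7 allergy, parathyroidectomy and outside vitamin K do not end outcome collection, which stops only at death or withdrawn consent. This changes no clinical stopping rule.

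Section 5 reports that visits are complete, so the remaining steps concern the analysis:

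1. Include every existing 18-month scan in the arm to which the patient was randomised.
2. Report exits by arm and by reason.
3. Censor mortality and MACE at last known follow-up when that is before 18 months.
4. Label any analysis restricted to patients with V2 as a completer analysis.
5. Add a sensitivity analysis that imputes ln(CAC) by arm from baseline variables (ln baseline CAC, diabetes, cfPWV, dp-ucMGP), with departures from missing-at-random explored by delta adjustment. Exit reason should not be a predictor: if no terminated patient has a scan, its effect cannot be estimated.

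The cost is some rewording, modest extra analysis and, if values are missing, a less favourable label for the primary comparison.

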### Biomarker of sub-clinical vitamin K deficiency

3.6

Blood will be collected in an ethylenediaminetetraacetic acid tube, processed after withdrawal and stored at −80 °C as plasma before analysis at Coagulation Profile BV, Maastricht University, the Netherlands. In brief, plasma dp-ucMGP levels will be determined in a single run using the commercially available IVD CE-marked chemiluminescent InaKtif MGP assay on the IDS-iSYS system (IDS, Boldon). Both patient samples and internal calibrators will be incubated with magnetic particles coated with murine monoclonal antibodies against dp-MGP, acridinium-labelled murine monoclonal antibodies against ucMGP, and an assay buffer. The magnetic particles will be captured using a magnet and washed to remove any unbound analyte. Trigger reagents will be added; the resulting light emitted by the acridinium label is directly proportional to the level of dp-ucMGP in the sample^[36]^

### Measurement of aortic stiffness

3.7

Conduit arterial or aortic stiffness will be assessed using applanation tonometry (SphygmoCorVx, AtCor Medical, West Ryde, NSW, Australia)^[37]^ by trained technicians blinded to treatment assignment. This non-invasive technique uses a high-fidelity pressure transducer applied lightly over the carotid, femoral and radial arteries to obtain the following:

